#### **HANDLING OF MISSING DATA**

We do not expect a large number of missing data for any of the baseline characteristics. Variables with missing values will be clearly indicated in the descriptive tables. We will use multivariable survival models only if substantial differences in the distribution of baseline characteristics are observed. If multivariable survival models are needed, a separate category including women with missing values will be created for each variable.

#### **SENSITIVITY ANALYSES**

We will compare women assigned to SLNB and those assigned to omission of SLNB using an intention-to-treat approach. However, for the main endpoint, we will also report the per-protocol analysis, where women assigned to SLNB who did not receive SLNB will be excluded, as well as women assigned to omission of SLNB who receive SLNB.

#### **CLASSIFICATION OF PROTOCOL VIOLATION**

We will provide a description of reasons why women were excluded after randomization.

### **5.2. DATA ANALYSIS**

A description of first events, deaths and follow-up time will be provided in Table 2. Frequencies and percentages will be used to describe first events and deaths, while median with IQR will be used to describe follow-up time.

Survival curves will be estimated using the non-parametric Kaplan-Meier method (DDFS, DFS and OS). Differences in survival will be tested using the Log-Rank test, and the p-value of the test will be reported. Cumulative incidence of distant metastases and of axillary recurrences will be calculated in a competing risk framework: events other than distant metastases or axillary recurrences, respectively, will be treated as competing events. Differences in the cumulative incidence between arms will be evaluated by means of the Gray test, and the p-value of the test will be reported. For the analysis of DDFS, DFS and cumulative incidences, only the data on the first event will be used.

We will use multivariable survival models only if substantial differences in the distribution of baseline characteristics are observed. The univariate analysis will be considered as the main analysis in any case. We will possibly use multivariable Cox models if the proportionality assumption is verified. We will possibly use parametric accelerated failure time regression models if the proportionality assumption is not verified; different distributions will be tested, and the most appropriate will be chosen based on the Akaike's information criterion.

To evaluate the primary hypothesis of non-inferiority in DDFS, we will report the p-value for non-inferiority calculated at five years, based on the pre-specified margin of non-inferiority of 2.5%. This means that observations will be right-censored at five years to evaluate the primary hypothesis. With the assumptions specified in the sample size paragraph, non-inferiority is defined as a hazard ratio (HR) of less than 1.74 for no SLNB versus SLNB. Analyses will be performed using SAS software, version 9.4 (SAS Institute Inc., Cary, NC, USA). All tests will be two-sided.

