### **Hypothesis of the study**

There are several concepts behind this study. First the acknowledgement that imaging is playing a crucial role in the present and in the future of oncology. Secondly, we are convinced that decisions on adjuvant systemic treatment should be taken considering the biology of the disease rather than the risk of recurrence as this attitude reflects an higher probability for the patient to benefit from a certain type of treatment. Finally, a less invasive surgery associated to a more tailored medical approach is aimed at improving patients' quality of life.

The hypothesis of this trial are that:

- ✓ avoiding axillary surgery is not worsening outcome of patients with small breast cancer
- ✓ the absence of the pathological information on the risk of recurrence given by nodal status is not worsening outcome of these patients
- ✓ pre-operative imaging of the axilla can identify patients with clinically relevant nodal burden

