The primary endpoint will be the DDFS, defined as the time free of both distant recurrence and death from any cause. If a patient have simultaneous locoregional and distant recurrences, she will be considered as having a distant recurrence in the analysis. Local recurrences, regional recurrences, contralateral breast cancers and other non-breast primary tumours will be considered as censoring events. The log-rank test will be used to test differences in DDFS. Secondary endpoints will be the cumulative incidence of distant recurrences, the cumulative incidence of axillary recurrences, the disease free survival (DFS) and the overall survival (OS). Differences in the cumulative incidence will be evaluated in a competing risk framework (15) by means of the Gray test (16), while differences in DFS and OS will be evaluated by means of the Log-rank test. Multivariable Cox regression models will be applied to adjust the risk estimates of interest for other variables. The Chi-square test for trend, Chi-square test and the Fisher exact test will be used to evaluate

differences in percentages between the two treatment groups, as appropriate. The T-tests will be used to evaluate differences in means for continuous variables.

All analyses will be carried out with the SAS software (SAS Institute, Cary, NC) and the R software (The R Development Core Team 2004; Free Software Foundation, Boston, MA). All tests will two-sided. The calculation of sample size was carried out using PASS software, based on method given in Jung SH et al. (17).

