## 1. STUDY OBJECTIVES

### 1.1. PRIMARY OBJECTIVE

To verify whether, in patients with small breast cancer, and in presence of a negative preoperative axillary assessment, SLN can be spared without worsening the prognosis

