## 2.4. SAMPLE SIZE

Women with pT1 tumours and negative axillary ultrasound will be randomized to receive either SLNB or no treatment in the axilla. We will consider women who will undergo SLNB as the reference group, and we will test for non-inferiority the group of women not undergoing any treatment in the axilla. The primary endpoint will be distant disease-free survival (DDFS) after randomization, with distant metastases and deaths from all causes counted as failures. For the purpose of sample size calculation, the 5-year DDFS in the reference group is assumed to be 96.5%. This estimate was obtained from the analysis of 2218 women with pT1, cN0, M0 tumours who underwent surgery (with SLNB) at the European Institute of Oncology from 01/01/2003 to 31/12/2005.

Overall, 1560 women (780 per arm) will be enrolled to decide whether the group without treatment of the axilla is no worse than the reference group, given a margin  $\alpha$  of non-inferiority of 2.5% (maximum tolerable 5-years DDFS = 94% ). Statistical power and one-sided type I error are set to 80% and 5%, respectively.

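### SAP 5.2 compares axillary recurrence between arms by a Gray-test p-value, with no between-arm difference or confidence interval, so a non-significant result could not by itself support a statement of no increase

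*Supplement*

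**What the plan says.** The aim is framed as absence of harm. SAP 1.1 asks whether "SLN can be spared without worsening the prognosis", and the protocol's hypothesis is that "avoiding axillary surgery is not worsening outcome of patients with small breast cancer".

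Only DDFS is given a non-inferiority margin (2.5 points at five years, or a hazard ratio below 1.74) and a power statement. Under SAP 4.1, a regional recurrence, axillary recurrence included, is a censoring event for DDFS.

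Axillary recurrence is a secondary outcome (SAP 4.2), analysed with other events as competing events. SAP 5.2 gives the comparison: "Differences in the cumulative incidence between arms will be evaluated by means of the Gray test". The p-value is reported, and all tests are two-sided. The protocol's statistical section plans the same: "by means of the Gray test (16), while differences in DFS and OS will be evaluated by means of the Log-rank test". For DFS and OS the SAP says "Differences in survival will be tested using the Log-Rank test, and the p-value of the test will be reported".

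SAP 5.2 also plans the cumulative incidence of axillary recurrence in each arm, and a Table 2 of first events with frequencies and percentages. Neither document names a between-arm contrast or a confidence interval for axillary recurrence.

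**The concern.** The protocol's summary says that nodes are removed for staging and to improve regional control, so regional failure is the most direct way in which omission could do harm. The primary endpoint does not count it as an event, which makes axillary recurrence the most specific measure of that harm.

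A test of equality answers whether a difference has been demonstrated. It does not show how large an increase has been ruled out. With about 20 to 50 events in total, a p-value above 0.05 is compatible both with no effect and with a doubling. What is at stake is the sentence on axillary control that will stand beside the DDFS result. With a p-value and two percentages the reader cannot see which excess is excluded; with an interval for the difference the reader can.

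**Working it through.** **The plan's own figure.** The SAP states "Overall, 1560 women (780 per arm) will be enrolled", "Statistical power and one-sided type I error are set to 80% and 5%, respectively", and that "the 5-year DDFS in the reference group is assumed to be 96.5"%. The margin as a hazard ratio is ln(0.94)/ln(0.965) = 1.737, which matches 1.74. Events needed: 4 × (1.645 + 0.842)² / (ln 1.737)² ≈ 81.2. With exponential survival, 5 years of uniform accrual and 5 more years of follow-up, the mean event probability at the reference rate is about 0.052. So N ≈ 81.2/0.052 ≈ 1562, against 1560 stated. The size reproduces, and it was set for DDFS alone.

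**Inputs for axillary recurrence.**
- 780 per arm (SAP 2.4).
- Two-sided test (SAP 5.2). The 5% level is my assumption, since none is stated for secondary outcomes.
- Rates quoted in the protocol's introduction: 0.9% at a median of 48 months after a negative SLNB; 0.9% at a median of 6.3 years with positive sentinel nodes and no dissection; 1.6% at a median of 5 years with untreated micrometastases. No rate is stated for the trial arms, so these serve as assumed control rates.
- Follow-up: five years per patient (the follow-up form schedule), or 5 to 10 years if everyone is followed to five years after the last entry (SAP 2.1).

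**Closed-form check, 5-year horizon.** For control rate p against 2p, with mean rate m = 1.5p:

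SE0 = √[2m(1−m)/780]; SE1 = √[(p(1−p) + 2p(1−2p))/780]; power = Φ[(p − 1.96·SE0)/SE1].

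At p = 0.009: SE0 = 0.00584 and SE1 = 0.00584, so the argument is (0.009 − 0.01145)/0.00584 = −0.42. Power is 34% and the miss rate 66%.

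| Control rate | Expected events (780 × 3p) | Doubling missed, two proportions | Doubling missed, Schoenfeld |
|---|---|---|---|
| 0.71% (0.9% × 5/6.3) | 16.6 | 72% | 71% |
| 0.9% | 21.1 | 66% | 64% |
| 1.125% (0.9% × 5/4) | 26.3 | 59% | 57% |
| 1.6% | 37.4 | 46% | 43% |

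An exact conditional test is more conservative: 74% missed at 0.9% and 53% at 1.6%.

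**Simulation of the Gray test.** Constant hazards, competing events 10% at 5 years in both arms (assumed), no dropout, 3000 trials per scenario, Monte Carlo error about 1 point. With equal rates of 0.9% the test rejects 5% of the time, as it should.

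| Rates at 5 years | Missed, cut at 5 years | Missed, 5-10 years |
|---|---|---|
| 0.9% vs 1.8% | 68% (about 20 events) | 55% (about 29 events) |
| 1.125% vs 2.25% | 59% | 49% |
| 1.6% vs 3.2% | 45% | 31% |

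**What an interval would show.** Take 7 against 16 axillary recurrences among 780 each. The difference is 9/780 = 1.15 points and the pooled z is 0.01154/0.00610 = 1.89, so p = 0.059. The unpooled SE is 0.00610, so the 95% CI is 1.15 ± 1.19, that is −0.04 to 2.35 points. The p-value reads as not significant, while the interval says that an excess of more than two points is not excluded. With 7 against 7, the 95% CI for the ratio is exp(±1.96·√(2/7)), or 0.35 to 2.85, and the upper limit for the difference is about 0.9 points.

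**The case against.** The strongest reply is that this is a rare secondary outcome in a trial powered for DDFS, and that lack of a margin or of power for such an outcome is ordinary. That stands. The absence of a margin for axillary recurrence is not the fault, and the fix does not supply one. In absolute terms the doubling is also small: +0.9 points from 0.9%.

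Some stronger readings are tempting, but the documents do not support them:
- A reader might infer that the p-value is the only information planned. It is not. Arm-level cumulative incidences and first-event counts will be visible; what is missing is the contrast and its precision.
- A reader might infer that the sponsor will treat non-significance as proof of preserved axillary control. No passage sets that rule. None guards against it either.
- A reader might infer that regional harm can show up nowhere else. DFS counts regional recurrences as events and OS counts all deaths. Axillary recurrence is the most specific measure, not the sole one.
- A reader might take 55-68% as the miss rate. It belongs to an assumed 5-year control rate of 0.9%. At 1.6% the test would detect a doubling more often than not.

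The protocol also mentions multivariable Cox models for adjusted risk estimates, which could give a ratio with an interval. The SAP, however, uses multivariable models only if baseline characteristics differ substantially, and names no interval for this outcome.

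For OS the argument is weaker. If control OS were 97.3% at 5 years (the protocol's micrometastasis cohort, a different population), the log-rank test would miss a 2.5-point loss in only 28% of trials at 5 years and 14% with 5-10 years.

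**Conclusion.** The concern holds as a weakness in the method of inference for axillary recurrence. It does not touch the primary DDFS analysis. Under the assumptions given (780 per arm, two-sided 5%, constant hazards, no dropout, quoted rates of 0.9% to 1.6% taken as 5-year control rates), the planned test misses a doubling roughly 30-70% of the time. Scaling the 6.3-year figure down to 5 years gives 72%, slightly above that range. No scenario computed here reaches 80% power for a doubling. A non-significant Gray test therefore could not, by itself, support a statement that omission does not increase axillary recurrence. An estimate with an interval, from the same data, shows how far such a statement can go. Weight: should be changed; it is cheap, and it alters what can be concluded about regional control.

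**What to change.** In SAP 5.2, for axillary recurrence:
- report the 5-year cumulative incidence in each arm (Aalen-Johansen) and the difference, no SLNB minus SLNB, with a 95% CI;
- base any statement on axillary control on that interval, in particular on its upper limit;
- state in advance that a non-significant Gray test is not evidence of no increase;
- keep the Gray p-value as supplementary.

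As a secondary point, give hazard ratios or 5-year differences with CIs for DFS and OS, and the difference in 5-year cumulative incidence with a CI for distant metastases, beside the planned p-values.

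The cost is SAP wording and a few lines of standard code on data already collected. The report would have to say which excess is excluded rather than that no significant difference was found, which is a more cautious message. No new margin, patients or visits are needed.

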## **SAMPLE SIZE CALCULATION AND STATISTICAL CONSIDERATIONS**

Women with pT1 tumours and negative axillary ultrasound will be randomized to receive either SLNB or no treatment in the axilla. We will consider women who will undergo SLNB as the reference group, and we will test for non-inferiority the group of women not undergoing any treatment in the axilla. The primary endpoint will be distant disease free survival (DDFS) after randomization, with distant metastases and deaths from all causes counted as failures.

For the purpose of sample size calculation, the 5-year DDFS in the reference group is assumed to be 96.5%. This estimate was obtained from the analysis of 2218 women with pT1, cN0, M0 tumours who underwent surgery (with SLNB) at the European Institute of Oncology from 01/01/2003 to 31/12/2005.

Overall, 1560 women (780 per arm) will be enrolled to decide whether the group without treatment of the axilla is no worse than the reference group, given a margin  $\Delta$  of non-inferiority of 2.5% (maximum tolerable 5-years DDFS = 94%). Statistical power and one-sided type I error are set to 80% and 5%, respectively.

The accrual period for the experimental study phase will be 5 years, and the additional follow-up years after the last entry will be 5 years. After 3 years from the start of accrual an interim safety analysis will be performed. If the 99% lower confidence bound for the hazard ratio of DDFS is  $> 1.0$ , the trial is stopped and the experimental treatment is declared inferior to the standard treatment (14).

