## DATA SUBMISSION - CASE REPORT FORMS SCHEDULE

| Form code | Type of Form                                  | Schedule                                                        |
|-----------|-----------------------------------------------|-----------------------------------------------------------------|
| FORM 1    | Verification of eligibility and Randomization | To fill in before randomization procedure                       |
| FORM 2    | Medical history                               | To fill in within two month from date of surgery                |
| FORM 3    | Axillary ultrasound/ Fnac                     | To fill in within two month from date of surgery                |
| FORM 4    | Surgery                                       | To fill in within two month from date of surgery                |
| FORM 5    | Suggested adjuvant therapy                    | To fill in within two month from date of surgery                |
| FORM 6    | Follow-up                                     | To fill in every six months for five years from date of surgery |

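### Censoring the primary hazard-ratio test at five years leaves about 55 events, not the 81 behind the sample size, so power is about 65% rather than the stated 80%

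*Supplement*

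**What the plan says.** SAP 2.4 repeats the design of the latest protocol. It states that "the 5-year DDFS in the reference group is assumed to be 96.5" per cent, that the lowest tolerable value in the no-surgery arm is 94% (a margin of 2.5 points), and that "Overall, 1560 women (780 per arm) will be enrolled". It adds: "Statistical power and one-sided type I error are set to 80% and 5%, respectively".

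The protocol's sample size section plans five years of accrual and says that "the additional follow-up years after the last entry will be 5 years". SAP 2.1 repeats this, with follow-up until 2022. The protocol names the method: PASS software, for a two-sample non-inferiority log-rank test. Neither document states a number of events.

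SAP 5.2 then sets out the primary test. It promises a non-inferiority p-value at five years based on the 2.5-point margin and explains: "This means that observations will be right-censored at five years to evaluate the primary hypothesis". It goes on: "non-inferiority is defined as a hazard ratio (HR) of less than 1.74 for no SLNB versus SLNB".

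The protocol's table of trial parameters ends at month 60, and its schedule for the follow-up form (Form 6) reads: "To fill in every six months for five years from date of surgery".

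**The concern.** The power of a log-rank or hazard-ratio test depends on the number of events. The planned follow-up runs to five years after the last entry, so a woman enrolled at the start would be observed for about ten years. If the sample size counted events from years 5 to 10, a test that discards them cannot have the power claimed for it.

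This is the primary hypothesis. In a non-inferiority trial, lost power means a higher chance of failing to show non-inferiority when omitting surgery is in fact no worse. A reader who trusts the stated 80% could take such a failure as evidence against omission when it partly reflects unused events.

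**Working it through.** **Inputs.** Five-year DDFS 96.5% against 94%, one-sided 5%, 80% power, 780 per arm (SAP 2.4 and protocol sample size section). Five years of accrual plus five (protocol; SAP 2.1). Five-year cut and hazard-ratio limit of 1.74 (SAP 5.2). Assumptions: exponential times, uniform accrual, true hazard ratio 1, no loss to follow-up.

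**1. Margin as a hazard ratio.** ln(0.94)/ln(0.965) = 1.737, which agrees with the SAP's 1.74. Its logarithm is 0.552.

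**2. Events required.** 4 × (1.645 + 0.842)² / 0.552² = 81.2.

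**3. Reproducing the plan's 1560.** The hazard is −ln(0.965)/5 = 0.00713 per year. With follow-up uniform on 5 to 10 years, the mean event probability is 1 − (0.965 − 0.965²)/(−ln 0.965) = 0.0520. Then N = 81.2/0.0520 = 1561, against 1560 stated. At 1560 women, 81.1 events are expected and power is 80.0%.

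**4. Could five years per woman give 1560 instead?** No. The event probability would be 0.035, so N = 81.2/0.035, or about 2320. Other standard event formulas do not change this:

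| Formula | Events | N, 5–10 years each | N, 5 years each |
|---|---|---|---|
| Schoenfeld | 81.2 | 1561 | about 2320 |
| Score form | 79.1 | 1522 | about 2260 |
| Freedman | 86 | about 1654 | about 2457 |

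**5. Power of the test in SAP 5.2.** Expected events with the cut are 1560 × 0.035 = 54.6. Power = Φ(√54.6/2 × 0.552 − 1.645) = Φ(0.394) = 65%.

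**6. Simulation.** Runs of 4000 trials per setting, using Wald and score forms of the test, gave 64% to 67% with the five-year cut and 79% to 80% with full follow-up.

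**7. What it takes to pass.** The upper one-sided 95% limit must fall below 1.737, so the estimate must fall below exp(0.552 − 1.645 × 2/√events). That is about 1.11 with 54.6 events and about 1.21 with 81.1.

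**8. Sensitivity.** These rates are assumptions, not figures from the documents:
- 5% of women excluded after randomisation: 1482 × 0.035 = 51.9 events, power 63%.
- 5% to 10% censored by year five at locoregional recurrences or second cancers: 53 to 52 events, power 64% to 63%.

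**9. The alternative scale.** For a five-year difference tested against 2.5 points, the standard error is √(2 × 0.965 × 0.035/780) = 0.00931. Power = Φ(0.025/0.00931 − 1.645) = 85%.

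**The case against.** The strongest reply is that SAP 5.2 speaks of a p-value at five years based on the 2.5-point margin, and gives 1.74 only as the translation of that margin. If the p-value came from a five-year Kaplan-Meier difference, power would be about 85% and nothing would be lost. The wording does not fully exclude this. But the sentence that defines non-inferiority does so by the hazard ratio, and the SAP names no difference test, variance or interval. A plan that allows 65% or 85% for its primary test still has to choose.

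A second reply is that SAP 5.2 also calls all tests two-sided, so one-sided 5% is itself in doubt. That is so, but it does not rescue the 80%: with 2.5% in the tail, the hazard-ratio test with the cut has about 53% power. I use one-sided 5% because the sample size section states it and because it reproduces 1560.

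Third, the cut is defensible. The margin is set at five years, and the cut neither inflates the type I error nor alters the margin; the confidence interval will show the lost precision. All of that stands. It justifies keeping the cut, but not keeping the 80% beside it.

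Finally, the cut applies only to the primary hypothesis. The survival curves, log-rank tests and Gray tests carry no such limit, so later events are not discarded everywhere. They are still not systematically collected, because the visit table and Form 6 stop at five years.

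**Conclusion.** The concern holds. The stated 80% belongs to an analysis of all follow-up over 5 to 10 years. The hazard-ratio criterion in SAP 5.2, applied to data cut at five years, has about 65% power at the stated one-sided 5%, with 54.6 expected events instead of 81.1. With identical arms it would fail about 35% of the time rather than 20%.

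The 81 events are derived, not stated, but they match the plan's sample size to within one or two women. The result assumes a constant hazard (beyond year five for the 81), equal arms, no loss to follow-up and a test on the hazard-ratio scale. Exclusions and extra censoring would lower power further. Because the primary test is affected and the choice of remedy should not depend on the results, this must be settled before the arms are compared.

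**What to change.** Choose one option and write it into both SAP 2.4 and SAP 5.2.

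- **(a) Keep the five-year cut and the 1.74 criterion**, and restate the power as about 65% with about 55 expected events. This costs only wording and a less favourable figure.
- **(b) Drop the cut for the hazard-ratio test** and use all follow-up to the 2022 cut-off, as the calculation assumed. Form 6 data and vital status must then be obtained past month 60 to that date, and the protocol's visit table and form schedule reconciled with its planned follow-up. The SAP is dated October 2022, so much of this would be retrospective retrieval for women enrolled early. The hazard ratio tested would then cover 5 to 10 years rather than five.
- **(c) Test the five-year DDFS difference directly against 2.5 points.** Name the estimator, variance and one-sided level, and state the power of about 85%. No new data are needed, but if the hazard ratio was the intended criterion this changes the scale of the primary test. It should be documented as such before any comparison of the arms.

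Whichever is chosen, SAP 5.2 should say which statistic yields the non-inferiority p-value and reconcile its two-sided statement with the one-sided 5% in SAP 2.4. None of the options needs further enrolment.
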